#### d. Study design: Cohort studies of *Schistosoma*-associated morbidity

**Overview:** The Cohort studies are sub-studies within SCORE Gaining Control studies, i.e., in communities with  $\geq 25\%$  prevalence of schistosomiasis during eligibility testing. They involve only Arms 1 and 6 of the Gaining Control studies, selected to represent the most intensive and a much less intensive intervention sequence, respectively (see below). Enrolled children were followed for five years, with evaluation occurring at Years 1 (baseline), 3 (after two MDA treatments), and 5 (after four MDA treatments).

**Cohort study design and expected sample size:** Cohort studies aimed to enroll 100 children from at least 4 communities/villages in each study arm, for a total of 800 children per study. The two Sh2 cohorts were discontinued: Mozambique because of significant loss to follow-up and Niger because of inappropriate randomization.

| Cohort Study | Year 1 | Year 2 | Year 3 | Year 4 |
|--------------|--------|--------|--------|--------|
|--------------|--------|--------|--------|--------|

[figure not shown]

Villages for inclusion in this study were meant to be a random sample of all the villages in the two study arms of interest (Arms 1 and 6); however, to facilitate the survey work investigators were allowed to select them randomly from among a restricted group of no less than 10 out of the 25 villages in each arm, chosen, for example, to exclude very remote villages.

The protocol called for selecting the 100-child cohort from the school class that starts at 7 or 8 years of age. If there were over 100 children in this class, children were to be randomly selected for participation. If this class did not include 100 children, then all of the children in that class should have been enrolled along with a random selection of children in the next older class, in order to reach the total of 100 study subjects.

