## V. DEFINITIONS OF PREVALENCE, INTENSITY, AND COVERAGE

The following definitions will be used for individual-level data:

- Individual mean eggs per gram (epg) (Sm studies):  $24 \times \text{total number of eggs found in all slides} / \text{number of slides examined}$ . Individual mean epg will be used for reporting, as it is the standardly used metric for infection intensity.
- Individual egg count (Sm studies):  $\text{Total number of eggs found in all slides examined} / \text{number of slides examined}$ . Individual egg count will be used for analysis, as epg does not have a continuous distribution. Note that some software packages may require individual egg count to be rounded prior to analysis. If the analysis requires integers, then the egg count used for formal statistical analysis should be  $6 \times \text{Total number of eggs found in all slides examined} / \text{number of slides examined}$ , rounded to the nearest whole number. If estimated counts are over 1,000 after adjustment for number of slides, they should be truncated at 1,000, as is common practice in schistosomiasis clinical research studies.
- Individual mean eggs per 10 ml (Sh studies):  $\text{Number of eggs found} \times 10 / \text{volume of urine filtered}$ . If estimated counts are over 1,000 after volume adjustment, they should be truncated at 1,000. Mean eggs per 10 ml will be used for both analysis and reporting, as this measure is both continuous and a standard metric. Note that some software packages may require mean eggs per 10 ml to be rounded prior to analysis, but this will only affect individuals with less than 10ml of urine filtered.
- Egg positive: a child will be deemed to be egg-positive if one or more eggs were found in any of the slides examined.

The following definitions will be used for reporting on cross-sectional and cohort studies:

- **Prevalence of *Schistosoma* infection:** Percentage of egg-positive children among the 9-12 year olds tested in each community each year.
- **Mean intensity of *Schistosoma* infection:** *Arithmetic* mean of individual mean epg or eggs per 10 ml among the 9-12 year-old children. Two values are to be reported:
  - i) Village-level intensity: This is the mean egg count for all tested 9-12 year-old subjects (including those with zero egg counts), which is a measure of community-level contamination potential.

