4. PedsQL scores (Total score and 4 subdomains: Psychosocial, Physical, School Performance, and Emotional) as continuous variables ranging from 0 to 100.
5. Liver patterns on abdominal ultrasound (categorical or ordinal scale).

Additional questions that could be explored relate to other ultrasound measures and whether the above measurements can be combined into a health and welfare score and be analyzed in regard to treatment arm.

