| (CI)                          |  |  |  |  |  |  |
| Mean hemoglobin in gm/dL (SD) |  |  |  |  |  |  |
| Prevalence of anemia % (CI)   |  |  |  |  |  |  |
| Mean Vo2 max score (SD)       |  |  |  |  |  |  |
| Mean PedsQL score (SD)        |  |  |  |  |  |  |
| Total Score                   |  |  |  |  |  |  |
| Physical                      |  |  |  |  |  |  |
| Emotional                     |  |  |  |  |  |  |
| Social                        |  |  |  |  |  |  |
| School                        |  |  |  |  |  |  |
| Liver pattern                 |  |  |  |  |  |  |
| B % (CI)                      |  |  |  |  |  |  |
| C or higher % (CI)            |  |  |  |  |  |  |

Tables 4 (multiple tables). Comparison between Arm 1 and Arm 6 of Year 5 morbidity outcomes.

For each outcome, the following type of table should be developed. The results should be as indicated in the cells below.

Example: Table 4A. Unadjusted and adjusted models for **anemia** at Year 5.

|                     | Unadjusted                   | Adjusted                   |
|---------------------|------------------------------|----------------------------|
| Arm (1 vs 6) | Parameter of Interest** (CI) | Parameter of Interest (CI) |
| Age          | ---                          | Parameter of Interest (CI) |
| Sex          | ---                          | Parameter of Interest (CI) |

*General approach to analysis:* For binary outcomes such as anemia status, the parameter of interest is typically the measure of association, such as odds ratio or relative risk. For models with other types of outcome, the parameter is the beta coefficient estimator from the corresponding models.

Generalized linear mixed effects models will be used to analyze the year 5 outcome. A generalized linear mixed effects model was chosen to account for random effects at the village level in year 5 comparison. The unadjusted model is a between-arm comparison without adjustment for other covariates. The adjusted model proposed here only includes adjustment for age and sex.

Generalized mixed effects models with normal, binomial, and multinomial distributional assumptions will be applied to address outcomes that are continuous, dichotomous, or categorical, respectively. SAS code examples for unadjusted models are provided below:

Sample code:

Linear mixed effects model code example

```
proc mixed;
  where Study_Year=5;
  class Person_ID Village_ID Study_Arm;
  model y = Study_Arm / solution;

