### c. Missing cohort data

We acknowledge that large numbers of children were lost to follow-up over the five years of the cohort studies. We will not attempt to impute values for them.

Regarding missing outcome data for those included in the cohort, in the primary analyses only children who have all the data needed to assess a particular outcome will be analyzed. In a secondary analysis, multiple imputation and sensitivity analyses will be used to check the robustness of the complete case analysis for outcomes that have 10% or more children without the data needed to conduct the specific analysis. The investigators involved in the Kenya and Tanzania cohorts and SCORE will work together to determine the optimal way to address the missing data issue in their respective datasets.

Preliminary checks on missing data percentages at baseline were conducted for Sm cohort datasets. The missing percentages for major variables were below the 10% threshold, except for PedsQL (12.7%) and some ultrasound variables. Ultrasound variables that are missing in  $\geq 10\%$  of children will not be included in any of the cohort analyses proposed in this SAP. Therefore, we anticipate that the small percentage of the analyses encountering missing data problems can be handled with multiple imputation. SAS programs used to check the missing data percentages are found in Appendix K: 'Additional SAS Code for Analysis of Cohort Data.'

The posterior distribution to be considered should reflect the noise associated with the uncertainty surrounding the parameters of the distribution that generates the data. Sensitivity checks will be conducted to ensure that the multiple imputation methods provide robust estimates. SAS codes and macros will be developed to conduct the multiple imputation and sensitivity analyses with pattern mixture models on the missing data. Some of the SAS programs developed for those purposes have already been included in the Appendix K: 'Additional SAS Code for Analysis of Cohort Data.'

**Table 6. Comparison of imputed and unimputed values for outcomes with  $>10\%$  missing data in Year 5 (from unadjusted models).**

| Outcome | Comparison Arm 1 vs. Arm 6 using raw data
(Complete-Case Analysis) | Comparison Arm 1 vs. Arm 6 using
multiple imputation |
|----------------|-------------------------------------------------------------------------------|-----------------------------------------------------------------|

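### A 10% missingness rule can remove liver pattern, a listed primary cohort outcome, from every cohort analysis, and the cohort's infection figures are defined for an age band that 7-8 year-old entrants have not reached at Year 1

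*Combined protocol and SAP*

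**What the plan says.** All references are to the main SAP.

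**Liver pattern.** Section VII.a lists as its fifth item of primary interest "Liver patterns on abdominal ultrasound (categorical or ordinal scale"). Cohort Table 3 has rows for pattern B and for C or higher. Other ultrasound measures appear only as questions that might be explored.

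**Missing data.** Section VII.c sets a general rule. The primary analysis uses children with complete data for the outcome. Where 10% or more lack the data needed, multiple imputation and sensitivity analyses follow. It then reports a check made at baseline: "The missing percentages for major variables were below the 10% threshold, except for PedsQL (12.7%) and some ultrasound variables". For ultrasound variables missing in 10% or more of children, it says they "will not be included in any of the cohort analyses proposed in this SAP". Table 6, in the same section, is for outcomes with more than 10% missing in Year 5.

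**PedsQL.** The outcome list in VII.a gives "Total score and 4 subdomains: Psychosocial, Physical, School Performance, and Emotional". Cohort Table 3 has rows for Total, Physical, Emotional, Social and School.

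**Infection in the cohort.** Section V says its reporting definitions serve both the cross-sectional and the cohort studies. It defines prevalence as "Percentage of egg-positive children among the 9-12 year olds tested in each community each year", and mean intensity uses the same ages. Section II.d describes "selecting the 100-child cohort from the school class that starts at 7 or 8 years of age", topped up from the next older class when there are fewer than 100 children.

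**The concern.** At one level of missingness the SAP prescribes two opposite actions: keep the outcome and test robustness by imputation, or discard it. Which applies depends only on whether the variable came from ultrasound, and no reason is given. Liver pattern is the only ultrasound outcome the SAP tabulates, so the rule could leave the planned Arm 1 versus Arm 6 comparison with nothing on liver morbidity. The visit is not fixed either. The Table 4 models use Year 5 data only, so gaps at baseline would not by themselves be a reason to drop that comparison.

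Section VII.a says the morbidity results must be read alongside prevalence and intensity in the two arms. If cohort prevalence is computed as section V defines it, the Year 1 and Year 5 figures describe different children. The change between them, and the egg reduction rate in cohort Table 2, would then partly reflect who was counted.

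The PedsQL mismatch is minor: one label differs between the outcome list and a descriptive table.

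**Working it through.** **1. The two missing-data rules side by side (section VII.c)**

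| | General rule | Ultrasound rule |
|---|---|---|
| Trigger | 10% or more missing | 10% or more missing |
| Primary analysis | complete case, outcome kept | variable dropped |
| Sensitivity analysis | multiple imputation and others | none |
| Visit for the trigger | not stated (baseline check reported; Table 6 refers to Year 5, with more than 10%) | not stated |

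PedsQL, at 12.7% at baseline, exceeds the trigger. No exclusion is written for it, so the general rule applies.

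**2. How sharp the cut-off is at the planned size**

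Section II.d gives 100 children × 4 villages × 2 arms = 800 per study, which reproduces the stated 800. The cut-off is then 0.10 × 800 = 80 children. PedsQL at 12.7% would be 0.127 × 800 = 101.6, about 102, if that percentage refers to one full cohort (an assumption, as no denominator is given).

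Let X be the number of children missing a variable, X ~ Binomial(800, p). The variable is dropped if X ≥ 80. The p values are an assumed range, because the documents give no missingness figure for liver pattern.

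| True missingness p | P(X ≥ 80) |
|---|---|
| 8% | 0.024 |
| 9% | 0.176 |
| 10% | 0.517 |
| 11% | 0.831 |
| 12% | 0.966 |

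This treats children as independent. Missingness that clusters by village would make the outcome of the rule less predictable near 10%. The table shows only that a hard cut-off can turn on a few children; it does not estimate what happened to liver pattern.

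**3. Age band**

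Nominal age at Year y = entry age + (y − 1). In band means 9-12.

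| Entry age | Year 1 | Year 3 | Year 5 |
|---|---|---|---|
| 7 | 7, out | 9, in | 11, in |
| 8 | 8, out | 10, in | 12, in |
| 9 (possible in the older top-up class) | 9, in | 11, in | 13, out |

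On these nominal ages, with four full years between the Year 1 and Year 5 surveys, no child counts at both: the youngest in-band age at Year 1 is 9, and 9 + 4 = 13. The number of children in each row is unknown.

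**4. PedsQL lists**

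Total, Physical, Emotional and School match. Psychosocial is only in the VII.a list and Social only in Table 3, so one of the four subdomain labels differs.

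**The case against.** **On liver pattern**, a reader might infer that it has been removed. The documents do not support that. The rule works variable by variable, and the text says only that the threshold was met "except for PedsQL (12.7%) and some ultrasound variables", without naming any. The SAP still plans for liver pattern: Table 3 has rows for it, and code for ordinal outcomes is given for both the Year 5 and the change models. The exclusion also depends on missingness, not on observed differences between arms. The SAP calls itself a minimum analysis and encourages more, and it asks the investigators and SCORE to agree how to handle missing data. All of this stands. It makes the loss conditional, but it does not explain why ultrasound is denied the route given to every other outcome.

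**On PedsQL**, a reader might infer that a primary subscale is never analysed, or that the set could be chosen once data are seen. Neither follows. Tables 4 and 5 are to be made for each outcome, and the VII.a list, which includes Psychosocial, fixes those outcomes. Only descriptive Table 3 departs from it.

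**On the age band**, the cohort text suggests all children were meant to be counted. Section III.b says every cohort child was to be tested in Years 1, 3 and 5. Cohort Table 1 has rows for the number in the cohort and the number tested, with no age filter. The individual egg-positive definition has no age limit. This is good evidence of intent, but section V expressly covers cohort reporting and nothing overrides it. A reader might also infer that the Year 1 group would be almost empty. No age distribution or top-up share is given, so that cannot be said.

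Cohort protocol B, data dictionary F, initial cohort plan J and code K are listed as appendices but are not in the supplied text. They might settle some of these points, though the body of the SAP would still conflict with itself.

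**Conclusion.** The point holds in a limited form.

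- **Liver pattern.** One of five primary outcome groups can be lost under a rule that contradicts the general rule in the same section. Whether it is lost depends on a missingness figure, and a choice of visit, that the documents do not give.
- **Infection figures.** Taken as written, section V excludes entrants aged 7-8 at Year 1 and includes them at Year 5; a child aged 9 at entry could be 13 and excluded at Year 5. This rests on the nominal entry ages and a four-year interval. It touches prevalence, intensity and egg reduction in cohort Tables 1 and 2. Infection is a secondary cohort marker, and no Table 4 or 5 morbidity model uses the definition.
- **PedsQL.** A label mismatch in one descriptive table, and clerical on its own.

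The first two deserve correction before the cohort analyses are reported. The third can be corrected at the same time.

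**What to change.** 1. In section VII.c, delete the ultrasound exclusion as it applies to liver pattern. Give liver pattern the rule used for other outcomes: complete-case primary analysis, with multiple imputation as a sensitivity analysis when 10% or more is missing. Judge the percentage on the year or years each analysis uses (Year 5 for Tables 4; Years 1 and 5 for Tables 5), state its denominator, and use the same inequality in the text and in Table 6. Report how much liver pattern data is missing at each visit, by arm and country.
2. In section V, define cohort prevalence and mean intensity among all cohort children tested that year, and limit the 9-12 restriction to the cross-sectional studies.
3. Use one set of PedsQL labels in section VII.a, Table 3 and Tables 4-5.

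The cost is SAP wording and a few more model runs. The downside is a less certain liver pattern estimate if missingness is high; setting the imputed result beside the complete-case one helps show how far the missing data matter.

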#### **d. Additional SAS code**

Additional SAS code that may be of use to individuals conducting analyses of cohort data are included in Appendix K.

## **VIII. PROTOCOL DEVIATIONS AND OTHER ISSUES**

A full listing of known protocol deviations is in Appendix L. One important issue relates to an underlying premise in the original design of the Sm2 and Sh2 studies, i.e., that well-conducted CWT would yield higher overall SAC treatment coverage and would prove more effective than other approaches. In Kenya, however, the CWT intervention in Year 1 was less intense than in the SBT arms because schools were not

used as treatment venues by the study teams. This will be commented on in the discussion of results but not adjusted for.

A second important issue of concern is that testing and MDA were supposed to occur on an annual basis. In some study locations, the agreed-to testing and treatment schedule was not reliably followed. A variable has been created to flag villages in which this occurred.

Several issues have arisen during the collection of the SCORE datasets. These include:

- Limited enrollment in some villages: The target study population size was 100 9-12 year old children. In some villages, the enrollment was significantly less. To account for this, a “village-weight” term will be added to the GEE model to weight results according to numbers of children tested per village.
- Truncation of Kato-Katz egg counts: In Kenya Sm1 and Sm2, egg counts were truncated at 42 eggs per slide in Years 1-3; they were truncated at 1,000 subsequently, which is more consistent with the laboratory practice used in other Sm clinical studies. We will not attempt to model the “true” egg counts for children with results recorded at the truncation level. We will present results indicating the recorded egg values and calculated egg values, and also categorized as no infection, and low, medium, or high-intensity infections.
- Missing data on some children
  - Children without data on age, sex, and presence or absence of eggs on at least one slide were not included in the study, with the exception of Mozambique, where 52 children (.9% of the total tested) are missing sex data in Year 1, and a smaller number are missing such data in later years. Children with missing sex data in Mozambique are largely from one village.
  - Issues related to some children having fewer slides than required by the protocol have been discussed elsewhere.
- Missing data are an issue for a limited number of variables in the cohort. This is discussed previously.

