#### a. Individual-level data in Gaining and Sustaining studies

Parasitological data on *Schistosoma* infection among children ages 9-12 were collected prior to each MDA and a year following the last treatment. No data were collected in villages during a holiday year.

In the Sm studies, duplicate Kato-Katz slides were made from each of three daily stool samples from each individual, and the number of eggs found in each slide was recorded. In the Sh studies, 10 ml of urine from a single well-stirred urine sample for each individual was filtered twice, and each of these two filtrations was examined under the microscope; the number of eggs found in each slide and the corresponding volume of urine filtered was recorded.

Parasitological data were also collected in Years 1, 3, and 5 on children in the first-year class and in Years 1 and 5 on adults (see Appendix D). However, given that data on these populations do not represent the

primary end-points of the SCORE treatment studies, and that the data collected on them are much more limited than that for 9-12 year olds, they will not be reported as primary end-points.

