| Village-level arithmetic mean* infection intensity at baseline           |                        |                        |                        |                        |                        |                        |
| Village-level arithmetic mean* infection intensity at Year 5             |                        |                        |                        |                        |                        |                        |
| Egg reduction rate (1-Year 5 intensity/baseline)                         |                        |                        |                        |                        |                        |                        |
| Individual-level arithmetic mean infection intensity at baseline*        |                        |                        |                        |                        |                        |                        |
| Individual-level arithmetic mean infection intensity at Year 5*          |                        |                        |                        |                        |                        |                        |

\*Taken as the mean of all per village means per arm, not the mean of all individuals in the arm

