  cluster="&cluster.";
  outcome="&outcome.";
  m=&m.;
run;
%mend;
```

```
%icc_bin(sac, HHID, asc, hhl, 2.91, stval=%str(), pred=%str());
```

Unadjusted intensity

The code is the same as for unadjusted prevalence, but the distribution and link are changed.

```
ods trace off;
proc genmod data=allyears descending;
  where Study_Year = 5;
  class Study_Arm Village_ID / param=glm;
  model Sh = Study_Arm / dist=nb link=log ;
  repeated subject=Village_ID / type=cs;
  lsmeans Study_Arm / cl;
run;
```

Adjusted intensity

The code is the same as for the adjusted prevalence, but the distribution and link are changed.

```
ods trace off;
proc genmod data=allyears descending;
  where Study_Year = 5;
  class Study_Arm Village_ID Sex Age / param=glm;
  model Sh = Study_Arm Sex Age / dist=nb link=log ;
  repeated subject=Village_ID / type=cs;
  weight villweight ;
  lsmeans Study_Arm / cl;
run;
```

Figure 4. Village-level mean intensity by year, by arm.

Provide a line graph showing arithmetic mean intensity, by Year, by Arm.

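### Kenya egg counts carry a lower cap in Years 1-3 than in Years 4-5, so the Table 3 egg reduction rate is understated and Figure 4 has an artificial upward break

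*Combined protocol and SAP*

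**What the plan says.** Section VIII of the main (Gaining and Sustaining) SAP, under protocol deviations, states: "In Kenya Sm1 and Sm2, egg counts were truncated at 42 eggs per slide in Years 1-3; they were truncated at 1,000 subsequently". It declines to model the true "egg counts for children with results recorded at the truncation level", and continues: "We will present results indicating the recorded egg values and calculated egg values, and also categorized as no infection, and low, medium, or high-intensity infections".

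Three required outputs nevertheless compare mean intensity across years:

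- Table 3 in section VI.b asks for baseline and Year 5 arithmetic means by arm and their ratio (row label "Egg reduction rate (1-Year 5 intensity/baseline").
- Figure 4 instructs: "Provide a line graph showing arithmetic mean intensity, by Year, by Arm".
- Cohort Table 2 in section VII.b asks for Year 1 to Year 5 intensity differences and the same reduction rate in Arms 1 and 6.

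None of these has a common cap, a Kenya exemption or a footnote. The metric is fixed in section V: "Individual mean epg will be used for reporting, as it is the standardly used metric for infection intensity". Section V also sets a general limit for the Sm egg count used in analysis: "If estimated counts are over 1,000 after adjustment for number of slides, they should be truncated at 1,000".

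**The concern.** A ratio of two means is interpretable over time only if both are measured by the same rule. Here the baseline mean has lost its upper tail and the Year 5 mean has kept most or all of it. Egg counts are strongly skewed, so that tail can hold much of the mean.

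At stake are the Kenya egg reduction rates in both Sm1 and Sm2 and the shape of the Kenya curves in Figure 4. In the sshh, cchh and shsh arms the change of cap falls across untested holiday years, so an artefact could be mistaken for rebound during a holiday. The SAP's preface seeks comparable country-level analyses and recommends combining the two Sm1 and the two Sm2 studies; Kenya belongs to both pairs.

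**Working it through.** **Inputs.** The caps come from section VIII. Section V gives epg = 24 x eggs / slides. Section III.a gives six slides per child ("duplicate Kato-Katz slides were made from each of three daily stool samples from each individual"). The arm sequences are in section I, and the rule of no testing in holiday years is in sections II.c and III.a.

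**Formula check.** The documents give no Kenya egg reduction rate to reproduce. Supplemental Table S6 for Niger confirms the formula: Group B, SSSS x2, 1 - 1.16/6.07 = 80.9%, as stated.

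**Caps on the epg scale.**

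- Years 1-3: 42 x 24 = 1,008 epg.
- Years 4-5, if 1,000 is per slide: 1,000 x 24 = 24,000 epg, which is 23.8 times the old cap.
- Years 4-5, if 1,000 is the section V cap on the integer scale (6 x mean eggs per slide): 1,000/6 = 166.7 eggs per slide, or 4,000 epg, about 4 times the old cap.
- If it meant 1,000 epg: 1,000/24 = 41.7 eggs per slide. That is nearly the old cap, so the change reported in section VIII would be no change.

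**Direction, with no distributional assumption.** Write B and Y for the baseline and Year 5 means, with the cap as subscript. B42 <= B1000 and Y42 <= Y1000. Hence 1 - Y1000/B42 is no greater than 1 - Y1000/B1000 and no greater than 1 - Y42/B42. The first inequality is strict once any baseline slide exceeds 42 eggs, the second once any Year 5 slide does.

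**Where Figure 4 breaks.**

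- ssss, cccc and ccss are tested every year: break between Years 3 and 4.
- sshh and cchh are tested in Years 1, 2 and 5: break between Years 2 and 5.
- shsh is tested in Years 1, 3 and 5: break between Years 3 and 5.

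**Size, by assumption.** Simulated six-slide counts used a gamma-Poisson spread between children (dispersion k = 0.1-0.4) with slide-to-slide variation:

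| Baseline to Year 5 (epg) | True reduction | Caps as recorded | 42 in both years |
|---|---|---|---|
| 200 to 60 | 70% | 47-65% | 55-65% |
| 300 to 90 | 70% | 36-60% | 51-62% |
| 100 to 50 | 50% | 33-48% | 41-48% |

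A second model used day-to-day variation and greater skew at Year 5. With a baseline of 300 epg, k = 0.25 and a true 50% reduction, B42 = 182, B1000 = 300, Y42 = 106 and Y1000 = 149. The recorded caps give 1 - 149/182 = 18.1%. A common 1,000 cap gives about 50%, and a common 42 cap gives 1 - 106/182 = 41.8%. Across that model's scenarios (baseline 50-500 epg) the shortfall against a common 1,000 cap ran from about 1 point (79.1% against 80.1%) to over 100 points (-51.6% against 49.4%).

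**Low-prevalence Sm1 villages.** The scenarios in the table imply 35-80% prevalence on two slides, whereas Sm1 villages were eligible at 10-24% on one stool with two slides. Matching 10-24% with k of at least 0.1 gives baselines of about 5-20 epg and a shortfall of 1 point or less. Heavier skew (k = 0.03-0.05, 20-50 epg) gives shortfalls of up to 28 points.

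**Outputs that withstand the change.** Egg positivity does not depend on the cap. The high category starts at 400/24 = 16.7 eggs per slide, below 42; in the second model the share in it moved by at most 0.6 points (for example 18.9% against 19.4%). Table 4 uses Year 5 only, so one rule covers all Kenya arms.

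**The case against.** The strongest reply is that the SAP discloses the truncation, reasonably declines to guess true counts, and commits to intensity categories. Figure 3 shows those categories by arm and year, so an over-time display that hardly depends on the cap is already required. Table 3 is descriptive, and the primary questions concern Year 5 differences between arms. All of that stands and limits the point to secondary summaries. It does not repair the reduction rate or Figure 4. Because the true counts will not be modelled, the promised calculated values cannot restore what the cap removed.

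A second reply is that a common 42 cap is itself biased. It is: 51-62% for a true 70% in one scenario. It does apply one rule to both years, and the direction argument shows it never gives a lower rate than the mixed caps.

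Readers might infer more than the documents support:

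- That Kenya's primary results are biased by the change of cap. Table 4 uses no baseline count.
- That both Kenya studies have already reported materially wrong reduction rates. No Kenya rate appears; Supplemental Tables S1 and S4 give only Year 5 between-arm ratios. The 36-65% figures do not describe typical low-prevalence Sm1 villages.
- That every arm shows a step from Year 3 to Year 4. The holiday arms were not tested in both of those years.
- That the later cap is certainly per slide. This is the natural reading, but the unit is not given.

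**Conclusion.** The point holds for Kenya Sm1 and Sm2 over-time intensity summaries: the Table 3 egg reduction rate and Figure 4, and also cohort Table 2 if the Kenya Sm2 cohort slides were read under the same rule. The direction is certain under either workable reading of the 1,000: the reduction is understated, and Figure 4 is shifted upward across the change of cap. The size cannot be derived from the documents, since it depends on baseline intensity and skew, which are not given. It could be negligible in Sm1 and tens of points in high-intensity villages. Prevalence, Figure 3 and the primary Year 5 ratios are essentially unaffected by the change of cap. This is worth correcting because the remedy is cheap, but it does not threaten the main comparison.

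**What to change.** 1. For Kenya Sm1 and Sm2, apply min(count, 42) to each Year 4-5 slide when computing the egg reduction rate, the Year 5 mean that enters it, and Figure 4. Do the same for cohort Table 2 if its slides followed the same rule.
2. Footnote those outputs with the rule and the share of slides at the cap by year and arm. State that a common 42 cap still understates the reduction when baseline counts are high, and that it does not make Kenya comparable with other countries.
3. Keep the 1,000-cap data for Table 4.
4. In section VIII, state the unit of the 1,000.

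The cost is one recode of slide counts already recorded, plus footnotes. The downside is that Kenya Year 5 means in Table 3 will be lower than those behind Table 4, which the footnote should explain.

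A separate minor point: section V applies 1,000 both to the per-slide count (24,000 epg) and to the six-slide integer count (4,000 epg). It should define the cap on one scale, so that it does not depend on whether the software needs integers.
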